### Participants timeline

All eligible residents for whom consent have been provided will be randomly allocated to the intervention group (individual music therapy) or control group (individual attention). Randomization will take place with a statistician using randomization software. The outcomes variables are measured at baseline (T0) one week before individual attention of music therapy starts (pre-treatment), after 6 weeks of intervention (T1) and after 12 weeks of intervention (T2). Figure 1 shows the participant’s flow.

**Fig. 1 Fig1:**
[figure not shown]
Participant flow: T0 baseline data collection, T1 follow up assessment at 6 weeks and T2 the follow up after 12 weeks. Participants who are lost to follow-up at the T2 assessment can still be included in the analyses, due to the use of mixed models analyses

Measurements (DS-DAT and PAIC-15) will be done at baseline T0, just shortly before (T1a and T2a) and shortly after the intervention (T1b and T2b); to assess overall effects, cumulative and immediate effects (**see** Table 1). An independent research assistant performs the blinded direct observations and complies the primary outcome well-being (measured with the DS-DAT) and secondary outcome pain (measured with the PAIC-15). The nursing staff will complete the unblinding observations scales concerning the various stages of dementia at baseline T0 and they will fill in the unblinding questionnaires about QoL, NPS, agitation and symptoms of depression at T1b and T2b.

Data prescription records concerning medication use, among which psychotropic drugs, will be extracted from the electronic medical charts by [name], physician employed by the participating organization.

**Table 1 Tab1:** Instruments at different assessment moments

Outcomes/instruments	T0 week 0	T1a (pre-treatment) Week 6	T1b (post-treatment) Week 6	T2a (pre-treatment) Week 12	T2b (post-treatment) Week 12
Primary outcome					
Well-being (DS-DAT)	X	X	X	X	X
Secondary outcomes					
Pain (PAIC-15)	X	X	X	X	X
Quality of life (QUALID)	X		X		X
Neuropsychiatric symptoms (NPI-NH)	X		X		X
Agitation (CMAI)	X		X		X
Depressive symptoms (CSDD)	X		X		X
Stages of dementia (GDS)	X				
Rest/activity (Actigraphy)	X				X
Medication use (ATC classification)	X				X

DS-DAT: Discomfort Scale - Dementia of Alzheimer Type, PAIC-15: Pain Assessment in Impaired Cognition, QUALID: Quality of Life in Late-Stage Dementia Scale, NPI-NH: Neuropsychiatric Inventory Nursing Home Version, CMAI: Cohen-Mansfield Agitation Inventory, CSDD: Cornell Scale for Depression in Dementia, GDS: Global Deterioration scale, ATC: Anatomical Therapeutic Classification system

### Sample size

The sample size calculation is based on the study’s primary outcome measure, the Discomfort Scale – Dementia of Alzheimer type (DS-DAT) [51] for F-tests ANOVA repeated measures. To determine the sample size required to assess relevant effects, we used data from the Cochrane review on music-based therapeutic interventions [27]; the effect size for emotional well-being and quality of life (SMD 0.32, 95%CI 0.02 to 0.62). The correlation between multiple assessments of the DS-DAT was calculated with the data of Schalkwijk et al. [57] as 0.6. Using a type I error of 0.05, a power of 0.80, two follow-up measurements and 2 groups, a sample size of 30 in each group is required, totaling 60 participants to achieve 0.81 power. According to the availability of music therapists we estimated that the study would take approximately 3 years. The mortality rate in the nursing home setting is high. Moore [58] stated that the length of stay in long-term care facilities in Europe countries is almost 2 years. It is estimated that about a one third (20 of 60 residents) may die or will be lost to follow up for other reasons during the study period, so we need to enroll a total of around 70 till 80 residents for this study.

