#### Data analysis

Immediate effects are defined as the difference in change between outcomes 15 min before and after the intervention sessions. Cumulative effects are effects over time not including those immediately after the session (i.e., built-up effect over time and measured before the session in order not to include possible immediate effects of the session). Overall effects are effects over time including those immediately after the session. Immediate, cumulative and overall effects are analyzed with mixed model analysis to consider the dependency of the repeated observations within the patient.

For the immediate effects, the outcome will be the post-test (T1b, T2b) and adjustment will be made for the pre-test (T1a, T2a). For the cumulative effect, the outcome will be the pre-test and an adjustment will be made for the baseline. For overall effects, the outcome will be post-test and adjustment will be made for the baseline.

For all treatment effects, effects at the different time-points will be analyzed by adding a time x treatment interaction to the mixed model analysis. Furthermore, both crude and adjusted (adjustments for gender, age, cognitive deterioration and for medication use, which will be added as a time-dependent covariate) will be performed. In the mixed-model analysis, we will also evaluate whether an adjustment for the correlated observations within facilities is necessary. There is no need to impute missing data because mixed models can handle missing assessments.

In explorative post-hoc analysis we will evaluate whether the intervention effects will be different for patients with a musical background by adding the interaction between the intervention variable and presence of musical background.

Sleep quality data of the MotionWatch (CamNtech Ltd, Cambridge, UK) will be analyzed with Motionware software version 1.2.1. Five parameters will be calculated: Interdaily stability, Intradaily variability, Relative Amplitude, most active period of 10 h and least active period of five hours. The 5 parameters will be analyzed with linear regression analyses with the values measured after the intervention period as outcome with an adjustment for the baseline vale of particular outcome.

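### The stated power of 0.81 at 60 participants comes from a different test than the planned baseline-adjusted model, which has power of about 0.45 at the stated SMD of 0.32

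*Protocol article*

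**What the plan says.** The Sample size section of the protocol article sizes the trial on the DS-DAT "for F-tests ANOVA repeated measures". It does not say whether the between-groups, within-subjects or interaction test was used. The effect comes from a systematic review: "the effect size for emotional well-being and quality of life (SMD 0.32, 95%CI 0.02 to 0.62". The repeated-measures correlation is 0.6, taken from a cited data set ("The correlation between multiple assessments of the DS-DAT was calculated with the data of" that study). Alpha is 0.05 and the target power 0.80; the remaining inputs and the result are: "two follow-up measurements and 2 groups, a sample size of 30 in each group is required, totaling 60 participants to achieve 0.81 power".

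The Data analysis section describes mixed models for three effects. Two of them use the baseline reading as a covariate: "For the cumulative effect, the outcome will be the pre-test and an adjustment will be made for the baseline", and "For overall effects, the outcome will be post-test and adjustment will be made for the baseline". The third, the immediate effect, adjusts for the reading taken before the same session. Effects at separate time points come from a time-by-treatment interaction.

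**The concern.** The two sections describe different statistics. In a between-groups repeated-measures ANOVA every measurement entered is an outcome, and the test compares the groups' averages over all of them. In the planned overall and cumulative models, T0 is a covariate and only the two follow-ups are outcomes. If T0 was one of the ANOVA's measurements, the calculation also assumed the full group difference before treatment, where randomisation makes it zero on average.

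The effect size is a second problem. An SMD is a difference in standard deviations (d), whereas the ANOVA routine takes Cohen's f, which for two equal groups is d/2. If 0.32 was entered as f, the assumed difference was 0.64 SD, twice the cited one.

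At stake is whether a reader can learn from the Sample size section what the trial's reported analysis is able to detect.

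**Working it through.** **Inputs.** From Sample size: SMD 0.32, correlation r = 0.6, alpha 0.05 (F-test, so two-sided in effect), N = 60, stated power 0.81. From Allocation: 1:1. From the primary outcome section and Table 1: occasions at baseline, week 6 and week 12. From Data analysis: baseline as covariate for the overall and cumulative effects. My assumptions: r = 0.6 holds between every pair of occasions, and the treatment effect is averaged over the two follow-ups.

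**Step 1: reproduce the printed figure.** Between-groups repeated-measures ANOVA with m measurements: λ = N f² m / (1 + (m − 1) r), referred to the noncentral F with 1 and N − 2 df.

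- f = 0.32, m = 3: λ = 60 × 0.1024 × 3 / 2.2 = 8.378; power 0.812. N = 58 gives 0.799, so 60 is the smallest even N for 0.80.
- f = 0.32, m = 2 (the stated two follow-ups): λ = 60 × 0.1024 × 2 / 1.6 = 7.68; power 0.778; 64 needed.
- f = 0.32, m = 4: power 0.830; 56 needed.
- f = 0.16 (the SMD converted), m = 3: λ = 2.095; power 0.296; 228 needed. With m = 2, power 0.276.
- Within-between interaction, f = 0.16: 0.778 (m = 2), 0.860 (m = 3).

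Of these variants only f = 0.32 with m = 3 in the between-groups test gives both 60 and 0.81.

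**Step 2: power of the planned model.** For the mean of k follow-ups adjusted for baseline, the residual variance in SD² units is v = (1 + (k − 1) r)/k − r².

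- k = 2: v = 0.8 − 0.36 = 0.44.
- k = 1 (single time point): v = 1 − 0.36 = 0.64.

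λ = N d² / (4v), with 1 and N − 3 df. At N = 60:

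| Difference d | λ, k = 2 | Power, k = 2 | Power, k = 1 |
|---|---|---|---|
| 0.32 (stated SMD) | 60 × 0.1024 / 1.76 = 3.49 | 0.451 | 0.331 |
| 0.64 (0.32 read as f) | 60 × 0.4096 / 1.76 = 13.96 | 0.957 | 0.861 |

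Against the printed figure: 0.81 − 0.451 = 0.359, so 36 points too high at the stated SMD; 0.81 − 0.957 = −0.147, so 15 points too low at d = 0.64. At d = 0.50 the planned model has 0.819, and the printed figure is about right.

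**Step 3: isolate the model mismatch.** Same d in both tests, N = 60:

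| d | ANOVA, m = 3 | Baseline-adjusted, k = 2 | Gap (points) |
|---|---|---|---|
| 0.10 | 0.073 | 0.089 | 1.6 |
| 0.20 | 0.144 | 0.209 | 6.5 |
| 0.32 | 0.296 | 0.451 | 15.5 |
| 0.48 | 0.569 | 0.787 | 21.7 |
| 0.64 | 0.812 | 0.957 | 14.4 |
| 0.80 | 0.945 | 0.996 | 5.1 |
| 1.00 | 0.994 | 1.000 | 0.6 |

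**Step 4: what 60 analysed can detect.** Power 0.80 with 1 and 57 df needs λ ≈ 8.12. Then d = √(4 × 0.44 × 8.12 / 60) ≈ 0.49 SD for the mean of the follow-ups, and √(4 × 0.64 × 8.12 / 60) ≈ 0.59 SD at a single time point. For 0.80 power at d = 0.32 the averaged effect needs 138 analysed.

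**The case against.** The strongest reply is that the model mismatch, taken alone, is conservative. At every fixed effect in Step 3 the planned model has more power than the sized test, and sizing on a less efficient test does not under-power a trial. That stands: the shortfall at the stated SMD comes from 0.32 apparently being entered as f. It does not rescue the printed figure, though. Correcting only the conversion inside the same ANOVA gives 0.30 power and a requirement of 228, against 138 for the planned model. Both corrections are needed.

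A second reply is that the protocol never says T0 was counted. That also stands. Three measurements is the only tried variant that matches both printed numbers, and the schedule has three occasions, but identifying the third as T0 is an inference. The mismatch does not depend on it, because the stated two measurements do not give 0.81 at 60 either.

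A third reply is that Data analysis describes three effects, not one, and does not name the average over follow-ups as its target. The variance of 0.44 indeed does not apply to the immediate effect, and the averaging and equal-correlation assumptions are mine.

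A reader who sees gaps near 15 points at both d = 0.32 and d = 0.64 might infer a constant discrepancy whatever the effect size. Step 3 rules that out: those two values lie on either side of a peak of about 22 points.

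**Conclusion.** The concern holds in a bounded form. The printed 0.81 describes neither the baseline-adjusted models for the overall and cumulative effects nor, read literally, an ANOVA with two measurements. For the SMD the protocol cites, planned power at 60 analysed is about 0.45 averaged over the follow-ups and 0.33 at a single time point. If 0.32 was meant as Cohen's f, planned power is 0.96 and the printed figure understates it; but the protocol calls 0.32 an SMD and gives no reason for a difference of 0.64 SD.

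These figures rest on a correlation of 0.6 between all pairs of occasions, an effect averaged over weeks 6 and 12, and 60 analysed. They do not cover the immediate effect. Nor do they show that the choice of ANOVA by itself weakened the trial.

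**What to change.** In Sample size, replace the ANOVA calculation with one for the baseline-adjusted model of the two follow-ups. Enter the SMD on its own scale (d = 0.32, f = 0.16) and do not count T0 as an outcome. Report power at 60 analysed (about 0.45), the difference detectable with 0.80 power (about 0.49 SD), and beside them the single-time-point power (0.33). State that r = 0.6 is assumed between every pair of occasions, and that the figures apply to the overall and cumulative effects because the immediate effect adjusts for the same-session reading.

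The cost is one recalculation and a rewritten paragraph. The restatement does not itself require a change in enrolment or conduct. The downside is a visibly less favourable power statement.

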**Methods:**

The research will be conducted at eight nursing home facilities of a health care organization in the Netherlands. A sample size of 30 in each group (experimental and control group) is required, totalling 60 residents increased to 80 when considering expected drop out to follow up. The participants in the intervention group receive 30 min of individual music therapy (MT) in their own room by a music therapist twice a week for 12 weeks. The participants in the control group will receive 30 min of individual attention in their own room by a volunteer twice a week for 12 weeks. Assessments will be done at baseline, 6 weeks and 12 weeks. An independent observer, blinded for the intervention or control condition, will assess directly observed well-being (primary outcome) and pain (secondary outcome) before and after the sessions. Nurses will assess other secondary outcomes unblinded, i.e., perceived quality of life and NPS, both assessed with validated scales. The sleep duration will be indirectly assessed by a wrist device called MotionWatch. Information about psychotropic drug use will be derived from electronic medical chart review.

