### Primary outcome measure

Observed well-being is the primary outcome measure rather than multidimensional quality of life with proxy estimation of domain ratings based on recall. Lawton has most extensively explored the concept of QoL concerning dementia and described QoL in dementia in terms of four sectors: psychological well-being, behavioral competence, objective environment (response to surroundings) and perceived QoL [46–48]. Jonker et al. reviewed conceptual developments in QoL research concerning dementia and based on the dimensions presented by Lawton, they identified psychological well-being as the core dimension of QoL of patients with dementia. Patients with severe dementia cannot always self-report their psychological well-being [49] but indicators of wellbeing of persons with dementia can be observed with validated instruments. We assess well-being with an objective observational instrument−the Discomfort Scale - Dementia of Alzheimer Type (DS-DAT) where discomfort is defined as a negative emotional and/or physical state subject to variation in magnitude in response to internal or environmental conditions. It is a scale for direct observation of behavior of a patient and is applicable also in later phases of dementia [50]. The Dutch translation is characterized by a good reliability (Hoogendoorn. 2001) [51] and validity (van der Steen, 2002) [52, 53]. The scale consists of 9 items measuring 7 negative and 2 positive items regarding vocalization, breathing, facial expression, and body movements. The nine 4-point items are summed for a total score ranging from 0 (no observed discomfort) to 27 (highest possible level of observed discomfort). Well-being will be assessed by a blinded research assistant at baseline (T0), six weeks (T1) and twelve weeks (T2). Well-being is assessed during 5 min before and after the music therapy sessions or individual attention sessions. The research assistant will be trained in using the DS-DAT trough an instructional video and practice completion of the DS-DAT with videotaped patients. Feedback is provided against the scores of the scale’s developer ([name]) who had rated the patient video clips.

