### Assignment of interventions

#### Allocation

Participants will be randomly assigned to either the control or the experimental group with a 1:1 allocation as per a computer-generated randomisation schedule. Randomization is performed by a statistician who is not involved in carrying out the study in the facilities, using randomization software.

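### 60 participants do not give 0.81 power for SMD 0.32: the figure matches 0.32 entered as Cohen's f, which doubles the effect

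*Protocol article*

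**What the plan says.** The Sample size section bases the calculation on the DS-DAT "for F-tests ANOVA repeated measures". Its effect size is "the effect size for emotional well-being and quality of life (SMD 0.32, 95%CI 0.02 to 0.62"). It adds that "The correlation between multiple assessments of the DS-DAT was calculated with the data of Schalkwijk et al. [57] as 0.6" and continues: "Using a type I error of 0.05, a power of 0.80, two follow-up measurements and 2 groups". The conclusion is that "a sample size of 30 in each group is required, totaling 60 participants to achieve 0.81 power". The abstract repeats the requirement: "A sample size of 30 in each group (experimental and control group) is required".

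The Primary outcome measure section schedules the DS-DAT "at baseline (T0), six weeks (T1) and twelve weeks (T2"), which is three occasions. Allocation is "with a 1:1 allocation as per a computer-generated randomisation schedule". The Sample size section mentions neither Cohen's f nor any conversion from the SMD. The Data analysis section plans baseline-adjusted mixed models rather than a repeated-measures ANOVA.

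**The concern.** An SMD is the difference between two group means in SD units. Cohen's f is the SD of the group means in the same units. With two equal groups the means lie half the difference either side of the centre, so f = SMD/2. Entering 0.32 as f therefore plans for an SMD of 0.64.

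The primary outcome's sample size rests on this figure. If the figure is wrong, the trial is presented as well powered for an effect that it would miss more often than it would find. A reader who trusts the stated 0.81 could then take a null result as evidence against the effect the trial was planned around.

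**Working it through.** **Inputs.** All come from the article: SMD 0.32, correlation ρ = 0.6, α = 0.05, two groups, N = 60 (Sample size); m = 3 occasions (Primary outcome measure); 1:1 allocation (Allocation). Sidedness is not stated; an F-test with these inputs is two-sided.

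**1. Reproducing the stated figure.** For the between-groups test in a repeated-measures ANOVA the noncentrality is

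λ = f² · N · m / (1 + (m − 1)ρ), with 1 and N − 2 degrees of freedom.

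With f = 0.32, m = 3, ρ = 0.6:

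- N = 60: λ = 0.1024 × 60 × 3 / 2.2 = 8.38, power 0.812
- N = 58: λ = 8.10, power 0.799

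So 60 is the smallest even total that reaches 0.80, and its power rounds to 0.81. Both stated figures match.

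**2. The same test with the SMD converted.** f = 0.32/2 = 0.16:

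- N = 60: λ = 0.0256 × 60 × 3 / 2.2 = 2.09, power 0.296
- 80% power: N = 228 (power 0.802; N = 226 gives 0.799), or 114 per group
- SMD detectable with 80% power at N = 60: about 0.63

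**3. Other readings with the printed inputs.** For the interaction test λ = f² · N · m / (1 − ρ).

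| Test | f | m | Power at N = 60 | Smallest N for 0.80 |
|---|---|---|---|---|
| Between groups | 0.32 | 3 | 0.812 | 60 |
| Between groups | 0.32 | 2 | 0.778 | 64 |
| Between groups | 0.16 | 3 | 0.296 | 228 |
| Between groups | 0.16 | 2 | 0.276 | 248 |
| Interaction | 0.16 | 2 | 0.778 | 64 |
| Interaction | 0.16 | 3 | 0.860 | 52 |
| Interaction | 0.32 | 2 or 3 | about 1.0 | 16 to 18 |

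Only the first row gives both 60 and 0.81.

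The interaction rows with f = 0.16 do not represent an SMD of 0.32 either. If the groups are equal at baseline and differ by 0.32 SD afterwards, then:

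- m = 2: the four interaction cell effects are ±0.32/4, so f = 0.08 and power is 0.276.
- m = 3: the group differences are 0, 0.32 and 0.32, with mean 0.2133. Halving the deviations from that mean gives cell effects of 0.1067, 0.0533 and 0.0533 in size. Then f² = (0.1067² + 2 × 0.0533²)/3 = 0.00569, f = 0.075 and power is 0.273.

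**4. The planned analysis.** For a baseline-adjusted comparison of the mean of two follow-ups, with equal correlation 0.6 throughout, the variance factor is (1 + ρ)/2 − ρ² = 0.80 − 0.36 = 0.44. With n per group, λ = SMD² · n / (2 × 0.44).

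- n = 30: λ = 0.1024 × 30 / 0.88 = 3.49, power 0.451
- 80% power for SMD 0.32: n = 69 per group (0.803; n = 68 gives 0.797)
- SMD detectable with 80% power at n = 30: about 0.49
- All 80 enrolled analysed, n = 40: power 0.57 (0.38 with the ANOVA of step 2)

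The correlation is printed to one decimal. At ρ = 0.55 the variance factor is 0.775 − 0.3025 = 0.4725 and power at n = 30 is 0.43. At ρ = 0.65 it is 0.825 − 0.4225 = 0.4025 and power is 0.48.

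**The case against.** **The cause is inferred.** The article does not name f, the software, the ANOVA term tested or the number of occasions entered. The match needs m = 3, whereas the section counts only two follow-ups. A rival route exists: an interaction test with f = 0.16, m = 2 and an unrounded ρ of 0.63 gives power 0.809 and a minimum of 60. With m = 3 and ρ = 0.6, a non-sphericity correction between 0.80 and 0.85 moves power from 0.798 to 0.815. This part stands: the f/SMD mix-up is the best explanation, not a documented fact. But the rival routes need inputs the article does not print, and they do not rescue the claim. An interaction f of 0.16 at m = 2 is a difference in change of 4 × 0.16 = 0.64 SD, again twice the cited effect.

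**The shortfall depends on the model.** The figures 0.30 and 0.63 belong to the stated ANOVA, which is not the planned analysis. Under the planned model the detectable SMD of 0.49 lies inside the review's interval of 0.02 to 0.62, so it would be wrong to say without qualification that the trial is powered beyond its evidence. This also stands. Averaging all four post-baseline DS-DAT readings would raise power to about 0.55 at 30 per group (variance factor 2.8/4 − 0.36 = 0.34). However, the Data analysis section models pre-session and post-session outcomes separately. Participants lost at T2 still contribute to the mixed model, yet full data on all 80 would give only 0.57.

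**The full protocol may hold the details.** It may, but the article prints both the inputs and a result that disagrees with them. Further detail cannot make 60 participants give 0.81 power for SMD 0.32 with the named test.

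**Conclusion.** The stated power is wrong as written. For SMD 0.32 and 30 analysed per group, power is about 0.30 with the stated ANOVA and about 0.45 with the planned baseline-adjusted model averaging two follow-ups. The claim of 0.81 is therefore too high by 0.51 or 0.36. With 80% power the trial detects an SMD of about 0.63 (stated ANOVA, just above the review's upper limit of 0.62) or about 0.49 (planned model, roughly 1.5 times the planning value).

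These figures assume ρ = 0.6 between all occasions, a two-sided 0.05 test and a constant effect at both follow-ups. The ANOVA figure of 0.30 also credits the effect to the baseline occasion, where none is expected, so it is generous. That 0.32 was entered as f is strongly supported but inferred; the shortfall holds whichever route produced the stated result.

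**What to change.** Correct the Sample size section and the matching sentence in the abstract, leaving enrolment as it is:

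- Remove the statement that 60 participants give 0.81 power for SMD 0.32, and the abstract's statement that 30 per group are required.
- State the effect-size metric, the test and the number of measurements used.
- State that 30 analysed per group give about 45% power for SMD 0.32 with the baseline-adjusted mixed model averaging two follow-ups (ρ = 0.6), and 80% power for an SMD of about 0.49.
- State that a non-significant result does not exclude SMD 0.32 and will be read from the confidence interval.

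The cost is wording in the protocol and SAP only. Treatment, measurements and analysis do not change. The price is a less favourable stated power.
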